**Parameter change (legend):**

Improvement: [figure not shown]  
No change: [figure not shown]  
Worsening: [figure not shown]

**Responder analysis (legend):**

Responder: [figure not shown]  
Non- Responder: [figure not shown]

|                     |                                                                                      |                                                                                     |                                                                                     |                                                                                     |                                                                                     |                                                                                     |                                                                                     |                                                                                     |                                                                                     |                                                                                     |
|---------------------|--------------------------------------------------------------------------------------|-------------------------------------------------------------------------------------|-------------------------------------------------------------------------------------|-------------------------------------------------------------------------------------|-------------------------------------------------------------------------------------|-------------------------------------------------------------------------------------|-------------------------------------------------------------------------------------|-------------------------------------------------------------------------------------|-------------------------------------------------------------------------------------|-------------------------------------------------------------------------------------|
| HbA 1c : | [figure not shown] |                                                                                     |                                                                                     |                                                                                     |                                                                                     |                                                                                     |                                                                                     |                                                                                     |                                                                                     |                                                                                     |
| Hypoglycaemia:      | [figure not shown] |                                                                                     |                                                                                     |                                                                                     |                                                                                     |                                                                                     |                                                                                     |                                                                                     |                                                                                     |                                                                                     |
| Insulin need:       | [figure not shown] |                                                                                     |                                                                                     |                                                                                     |                                                                                     |                                                                                     |                                                                                     |                                                                                     |                                                                                     |                                                                                     |
| Response:           | [figure not shown]  | [figure not shown] | [figure not shown] | [figure not shown] | [figure not shown] | [figure not shown] | [figure not shown] | [figure not shown] | [figure not shown] | [figure not shown] |

Per the above classification, a responder (X) is defined as a subject with:

- An improved HbA1c and an improved or unchanged hypoglycaemia, irrespective of insulin changes
- An unchanged HbA1c with an improved hypoglycaemia, irrespective of insulin changes
- An unchanged HbA1c and an unchanged hypoglycaemia with improved insulin requirements

Figure 7.3.2.2: 1 Summary of responder classification

Proprietary confidential information.

© 2012 Boehringer Ingelheim International GmbH or one or more of its affiliated companies. All rights reserved.

This document may not - in full or in part - be passed on, reproduced, published or otherwise used without prior written permission.

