### **2.3 BENEFIT - RISK ASSESSMENT**

The overall safety profile outlined in [Section 1.2](#) is favourable for human studies at chronic doses up to 50 mg/day. The maximum dose administered in the single rising dose study was 800 mg and the maximum dose for a 4 week treatment was 100 mg/day and both regimes

Proprietary confidential information.

© 2012 Boehringer Ingelheim International GmbH or one or more of its affiliated companies. All rights reserved.

This document may not - in full or in part - be passed on, reproduced, published or otherwise used without prior written permission.

were well tolerated. In Phase II, 12-week treatment duration Trials 1245.9 and 1245.10 in T2DM subjects, the maximum daily dose of BI 10773 was 50 mg. All doses of BI 10773 were well tolerated in these studies.

Because of the insulin-independent mechanism of action of BI 10773 and in light of the fact that GFR is physiologically decreased during episodes of hypoglycaemia (due to reduced renal blood flow hence leading to lowering of UGE and therefore efficacy of BI 10773), the risk of hypoglycaemic episodes with BI 10773 alone is considered to be low. A daily dose of 25 mg BI 10773 has been previously shown to result in urinary excretion of nearly 80 g of glucose every 24 hours. Hence, to adjust the daily insulin requirements in anticipation of the observed increased glucosuria, study subjects will be required to reduce their bolus insulin injections based on Table 2.3: 1 (below); this measure further limits the potential for hypoglycaemia to occur. The estimates for the anticipated required reduction in the amount of bolus insulin doses at the start of treatment (Day 3) are based on the 500 Rule (for Humalog or NovoLog) or the 450 rule (for regular insulin). As an added safety measure, subjects will also be required to decrease their insulin basal dose by 30% at the start of treatment in order to potentially prevent the possible risk of nocturnal hypoglycaemia (based on Table 2.3: 2). If subjects are on a different basal to bolus breakdown than the below examples, the correct reduction amount of basal and bolus insulin will be determined by the investigator.

Table 2.3: 1 Percent reduction in the amount of each daily bolus insulin injection to account for the daily urinary excretion of 80 grams of sugar

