| 60                                      | 8                                                         | 10.0                                               | 28%                                                                                                                         | 30%                    | 33%                    | 8                                                        | 1.3                                                | 28%                                                                                                                         | 30%                    | 33%                    |     |
| Average bolus reduction:                |                                                           |                                                    | 27%                                                                                                                         | 29%                    | 32%                    |                                                          |                                                    |                                                                                                                             | 29%                    | 32%                    | 35% |

Proprietary confidential information.

© 2012 Boehringer Ingelheim International GmbH or one or more of its affiliated companies. All rights reserved.

This document may not - in full or in part - be passed on, reproduced, published or otherwise used without prior written permission.

Table 2.3: 2                      The adjusted daily basal insulin amount (in units) for added safety based on a 30% reduction and per below basal to bolus breakdowns

| Total
Daily
Insulin
Dose
(TDD) In
Units | Adjusted daily basal insulin
amount (units) for added safety
based on a 30% reduction and per
below basal to bolus breakdowns |                        |                        |
|--------------------------------------------------------|----------------------------------------------------------------------------------------------------------------------------------------|------------------------|------------------------|
|                                                        | 40% Basal
60% Bolus                                                                                                                 | 45% Basal
55% Bolus | 50% Basal
50% Bolus |

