#### 4.2.1 Rescue medication, emergency procedures and additional treatments

During the screening and run-in period, subjects should continue to take the antidiabetic treatment they were receiving at informed consent as background therapy. The background insulin medication can remain unchanged or change partially or completely as per subject needs or based on the investigator's clinical judgement (treatment to target according to local guidelines is encouraged).

Insulin will not be provided as part of the clinical trial supplies.

To prevent the possible risk of hypoglycaemic episodes in subjects with T1DM on insulin therapy and BI10773, study subjects will initially be required to reduce their basal and bolus insulin injections by approximately 30% at the start of the treatment phase (one day after Visit 4 – study Day 3). All subjects must follow an appropriate investigator-recommended carbohydrate counting method and insulin titration algorithm during the course of the study in order to achieve optimal and individualized glycaemic goals. It is expected that insulin requirements will change during the course of the treatment phase and as such, each subject will have to titrate their insulin intake accordingly to prevent episodes of hyper or hypoglycaemia. Insulin dose adjustments should be done when feasible under the investigator's guidance. In addition, subject will have to test their blood glucose level at home several times a day as recommended by the investigator. Any insulin dose change or adjustment must be based on blood glucose measurements (not CGM data).

In case of hypoglycaemia, which may put a subject at risk (for example, repeated symptomatic hypoglycaemia or severe hypoglycaemia), appropriate reduction of ongoing background therapy (insulin) should be initiated in consultation with the investigator when feasible.

There are no special emergency procedures to be followed. There are no rescue medications in this trial. The patient's background insulin dose can change at any time in order to achieve the best standard of care.

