##### Other exploratory diabetes mellitus endpoints:

The other exploratory diabetes endpoints include:

- Change from baseline in HbA1c after 8 weeks of treatment with BI 10773
- Change from baseline in ~~glycated albumin (GA)~~ **fructosamine (FA)** after 8 weeks of treatment with BI 10773
- Change in fasting plasma glucose from baseline
- Change in glycaemic exposure, variability and stability as derived from Continuous Glucose Monitoring (CGM) from baseline
- Change in parameters of glucose variability (as measured by CGM or home blood glucose monitoring [HBGM])
- Change in mean daily glucose (as derived from the 8-p HBGM)
- Change in AUC for glucose (CGM data) from baseline
- Change in basal, bolus and total insulin requirement from baseline
- Change in basal insulin requirement day vs night from baseline
- Change in the numbers of bolus boosts from baseline
- Change in UGE from baseline
- Change in BP from baseline
- Change in the Diabetes Treatment Satisfaction Questionnaire from baseline

Proprietary confidential information.

© 2012 Boehringer Ingelheim International GmbH or one or more of its affiliated companies. All rights reserved.

This document may not - in full or in part - be passed on, reproduced, published or otherwise used without prior written permission.

- Change in HbA1c, hypoglycaemia and insulin requirements from baseline (refer to [7.3.2](#) for details of responder classification)

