Descriptive statistics will be used to summarize and evaluate the other diabetes-related endpoints. In addition, analyses will be performed to evaluate the follow-up period (Visits 14 and 15). These analyses will be performed on the FAS\_T1DM.

Proprietary confidential information.

© 2012 Boehringer Ingelheim International GmbH or one or more of its affiliated companies. All rights reserved.

This document may not - in full or in part - be passed on, reproduced, published or otherwise used without prior written permission.

Definition of responder for HbA1c, hypoglycaemia and insulin requirements:

Responder classification will be performed based on the change in HbA1c, hypoglycaemia and insulin requirements from baseline. The responder criterion will be defined as a composite of the following parameters:

- HbA1c change:
  - Improvement: Defined as  $\geq 0.3\%$  lowering relative to baseline
  - No change: Defined  $< 0.3\%$  lowering to  $> 0.3\%$  increase relative to baseline
  - Worsening: Defined as  $\geq 0.3\%$  increase relative to baseline
- Hypoglycaemia change:
  - Improvement: Defined as 30% lowering relative to baseline
  - No change: Defined  $< 30\%$  lowering to  $> 30\%$  increase relative to baseline
  - Worsening: Defined as  $\geq 30\%$  increase relative to baseline
- Insulin requirement change:
  - Improvement: Defined as 20% lowering relative to baseline
  - No change: Defined  $< 20\%$  lowering to  $> 20\%$  increase relative to baseline
  - Worsening: Defined as  $\geq 20\%$  increase relative to baseline

Details of responder classification are provided below (Figure 7.3.2.2: 1):

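### The 20% insulin criterion for response lies inside the Day 3 insulin cut of about 27-33% that the protocol itself requires, so the insulin-only responder route mixes instruction with drug effect

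*Protocol*

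**What the plan says.** **The mandated cut.** Section 4.2.1 states that "study subjects will initially be required to reduce their basal and bolus insulin injections by approximately 30% at the start of the treatment phase", that is, on Day 3. Section 2.3 gives the two parts. For basal insulin, "subjects will also be required to decrease their insulin basal dose by 30% at the start of treatment" (Table 2.3: 2). For bolus insulin, Table 2.3: 1 ends in a row headed "Average bolus reduction" with 27/29/32% under the 500 rule and 29/32/35% under the 450 rule, for bolus shares of 60/55/50%. The bolus cut is derived in advance from an assumed 80 g/day of urinary glucose, not from the subject's own response. For other basal:bolus splits the investigator sets the reduction. Section 4.2.1 also expects each subject to titrate insulin afterwards.

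**The responder rule.** Section 7.3.2.2 defines the insulin component as "Improvement: Defined as 20% lowering relative to baseline". Three routes lead to response:

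1. improved HbA1c with improved or unchanged hypoglycaemia, whatever happens to insulin;
2. unchanged HbA1c "with an improved hypoglycaemia, irrespective of insulin changes";
3. unchanged HbA1c and "an unchanged hypoglycaemia with improved insulin requirements".

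Unchanged HbA1c means a change of less than 0.3% either way, and unchanged hypoglycaemia means less than 30% either way.

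**Related endpoint and design.** Section 5.1.1 also lists "Change in basal, bolus and total insulin requirement from baseline" as an exploratory diabetes endpoint. Section 4.1.1 states that there is no comparator.

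**The concern.** The insulin component is meant to show that a subject needs less insulin. On the first treatment day, however, insulin falls because the protocol says so, and by more than the threshold. Any part of that cut still in place at assessment counts towards improvement, whether or not the drug made it possible.

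The second route is exposed too, since a lower insulin dose can itself reduce hypoglycaemia. No group had the same cut without the drug, so the data offer no way to subtract it.

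What is at stake is the reading of two descriptive efficacy results, the responder rate and the change in insulin requirement. Both serve the secondary objective.

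**Working it through.** **1. Reproduce the protocol's reductions.** Inputs: total daily dose (TDD) of 20 to 60 units, grams covered per unit, and bolus share, all from Table 2.3: 1; 80 g/day urinary glucose and the 30% basal cut from section 2.3.

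Bolus cut = (80 / grams per unit) / (TDD × bolus share). Averaged over the seven TDD rows:

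| Bolus share | 500 rule | 450 rule |
|---|---|---|
| 60% | 26.7% | 29.3% |
| 55% | 29.1% | 32.0% |
| 50% | 32.0% | 35.2% |

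These match the printed averages. Table 2.3: 2 equals 70% of the basal dose. In Table 2.3: 1, the 450-rule column of units needed (4.0 down to 1.3) equals 80/TDD and disagrees with its own grams-per-unit column, while the percentages beside it agree with grams per unit. The percentages are used here; the column must be reconciled.

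**2. Cut in total daily insulin.** Total cut = (80 / grams per unit + 0.30 × basal dose) / TDD.

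- Typical case (TDD 50, 50/50 split, 500 rule): (8.0 + 7.5) / 50 = 31.0%.
- Smallest (TDD 40, 60% bolus, 500 rule): (6.15 + 4.80) / 40 = 27.4%.
- Largest (TDD 40, 50% bolus, 450 rule): (7.27 + 6.00) / 40 = 33.2%.

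Every tabulated case passes the 20% threshold on Day 3, by about 7 to 13 points.

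**3. Titration needed before the component is lost.** Room to raise the reduced dose = 0.80 / (1 − cut) − 1. For a 30% cut: 0.80 / 0.70 − 1 = 14.3%. As a share of the cut: (30 − 20) / 30 = one third. For cuts of 27-33% the room is about 10-19%.

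**4. What the other two conditions remove.** This step rests on assumptions that are not in the protocol: an inert drug; SD of HbA1c change 0.3-0.5%; 1-3 hypoglycaemic events per week, varying between subjects (CV 0.5); a 2-week baseline and 2 or 8 treatment weeks; insulin change normal around −30% × fraction retained, with SD 12 points; 200,000 simulated subjects per setting.

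| Cut retained | Further assumption | Insulin component met | Insulin-only route | All routes |
|---|---|---|---|---|
| None | hypoglycaemia rate ratio 1, mean HbA1c shift 0 | 5% | about 1% (0.6-1.5) | 26-35% |
| Half | rate ratio 1, mean HbA1c shift 0 | 34% | 4-11% | 34-41% |
| All | rate ratio 0.7, mean HbA1c shift 0 to +0.1 | 80% | about 9-19% | 44-66% |

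Only the insulin-only column measures what the cut does through the third route. The all-routes column is mostly chance classification on HbA1c and hypoglycaemia. In the last row it also reflects the assumed fall in hypoglycaemia: with the rate ratio kept at 0.7 but the insulin effect removed, the rate is still 36-49%.

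**5. A larger HbA1c rise.** With the full cut, a rate ratio of 0.7 and a mean HbA1c rise of 0.5, the all-routes rate falls to 17-27%, below the no-cut figure.

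**The case against.** The strongest reply is that the cut satisfies one condition of three. HbA1c must not rise by 0.3% or more, hypoglycaemia must not rise by 30% or more, and subjects titrate after Day 3. A subject who holds 20% less insulin for 8 weeks with HbA1c and hypoglycaemia unchanged shows what a real insulin-sparing effect looks like. With an inert drug, a sustained 30% cut should push HbA1c up, and step 5 shows that the HbA1c condition then removes many subjects. This stands. It is why a reader should not infer that the cut alone makes a subject a responder, or that every treated subject passes the threshold: investigators set the reduction for splits outside the tables, and some subjects will titrate back above 80% of baseline.

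It does not close the matter. HbA1c may rise by anything short of 0.3% and still count as unchanged, and after a 30% cut two thirds of it can remain with the insulin component still met.

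A second reply is that the assessment window belongs in the statistical analysis plan, which is not at hand. That is fair, and the absence of a window is not the fault raised here. The conflict is between two figures that the protocol does fix, the 20% threshold and the cut of about 30%. A late window would narrow it but would not tell retained instruction from reduced need.

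Third, the endpoint is one of many exploratory ones, summarised descriptively in an open-label pilot, and the lack of a comparator is declared. This limits the weight of the point, not its truth.

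**Conclusion.** The point holds in limited form. For the tabulated splits, the insulin component is met by instruction on Day 3 and, after a 30% cut, stays met until more than one third of the cut is restored. The insulin-only route and the change in insulin requirement therefore combine the mandated cut with any drug effect, and the single-arm design cannot separate them.

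The likely size through the insulin-only route is modest: about 1%, 4-11% or 9-19% of subjects according to how much of the cut is retained, under the assumed inputs above. A reader might take the simulated all-routes rates of up to 66% as the size of the artefact. They are not: 26-35% arises with no cut at all, and the top figure depends on a rate ratio of 0.7 that the protocol does not supply.

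Two assumptions remain. The section 7.1 baseline list does not name insulin; a pre-Day 3 baseline is inferred because every baseline listed there precedes treatment. The insulin criterion is read as a lowering of at least 20%. The primary GFR analysis is unaffected. This should be corrected as a matter of definition and reporting for an exploratory efficacy result.

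**What to change.** In section 7.3.2.2:

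- **(a)** Assess the insulin and hypoglycaemia components over the last 2 weeks before Visit 12, against the 2-week run-in.
- **(b)** Report the responder rate split by its three routes, with the insulin-only route as a separate count, and note that the hypoglycaemia route may also reflect the mandated cut.
- **(c)** Summarise insulin change both from the run-in dose and from the mandated Day 3 dose, stating that the first includes the protocol-required reduction.

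The rate of worsening under mirrored limits should not be offered as a chance reference. With no effect and no cut it simulates at 35-40% against 26-35% responders, because ratios of small event counts are asymmetric.

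The cost is some wording and a few extra table rows, with no new data. The downside is a less favourable responder figure. No change to insulin dosing is implied.
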